#### Psychometrics

A set of well-known instruments with established validity and reliability was selected for psychometric testing in this study. For example, amongst the primary outcome variables of interest, concurrent validity with other tests of cognitive and motor skills such as the Wechsler Pre-School and Primary Scale of Intelligence (WPPSI-III) (range: *r *= .47, fine motor skills; *r *= .82 language skills), PLS-4 (range: *r *= .44 motor skills, *r *= .69 receptive communication) and the Peabody Developmental Motor Scale (range: *r *= .41, expressive communication; *r *= .57 motor skills) have been documented, while split-half internal consistency reliability of between *r *= .86 (fine motor coordination) and *r *= .93 (language skills), and test-retest reliability ranging from *r *= .80 (fine motor ability) to r = .87 (language competency) has been determined for the Bayley-III Scale [69]. Discriminant validity between normal and at-risk infants [79] and significant test-retest reliability (*r *= .44) across three occasions [80] has been reported for the NNNS; discriminant validity (depressed vs. non-depressed) and concurrent validity (compared with clinical assessment) has been demonstrated, while internal consistency reliability has been confirmed via both Cronbach's alpha and the Spearman-Brown split-half method, with estimates ranging between 0.85 and 0.9 for the CES-D Scale [54,81]. An exception is the Mom's Support Circle (Additional File 1) measure, which was devised specifically for the NICU study and has not yet been validated (See Table 1 for power analyses).

#### Blinding

##### Data coding and analysis

All data analyses are conducted on de-identified data, and assessments are made without knowledge of the mother and infant's group assignment whenever possible. Coding is performed by raters blinded to subject assignment.

##### Self-report assessments by mothers

Mothers in the two groups read and respond to self-report questionnaires independently and receive advice and consultation that may reduce anxiety and distress. However, it is not possible to blind mothers to group assignment because mothers in the intervention group are given extensive instruction in nurture activities and are given personal attention by the NS. In the course of receiving normal NICU care and attention, mothers in the SC group may observe FNI mothers receiving supplementary attention. Moreover, the infants in the two groups may occupy nearby isolettes. Thus, SC mothers may interact with FNI mothers and observe the FNI activities.

##### Objective assessments

Neurobehavioral assessments, including the NNNS and Bayley-III Scale, are conducted by clinical psychologists blinded to group assignment. Infant and mother physiological data (e.g., cardio-respiratory, EEG) is collected by non-blinded research assistants but coding, data reduction and preliminary data analysis is done without knowledge of group assignment. Only final group comparison analyses are, of necessity, performed with knowledge of group status.

### Confidentiality of Study Data

At recruitment, a subject is given a unique study number. All forms and data are identified by this number, rather than by the subject's name. Patient data are stored in locked cabinets and access is limited to the study staff. All data collected in this study are computerized, managed and stored under the oversight of the Data Coordinating Center at Columbia University College of Physicians and Surgeons, in a physical and electronically secure relational database management system using Scientific Information Retrieval (SIR) software.

## Discussion

Nurture may be viewed as the integration of multiple processes within the mother-infant dyad, from cognitive and emotional to physiological to molecular levels. The biobehavioral processes that comprise mother-infant interactions provide regulation for both members of the dyad. In very young animals and human infants, the biological systems regulated by nurture are those from which psychological/motivational and cognitive systems develop as the organism matures [82]. An emerging body of animal and clinical evidence is revealing the critical importance of specific mother-infant interactions on regulating the physiology and behavior of the infant in the short term, and for shaping the development of their adaptive behavior and physiology, extending into adulthood [82-86]. Our intervention is designed to activate these proximal mechanisms for the improvement of developmental outcome in premature infants. Changing these interactions during early development is known to have profound long-term effects on the development of the infant and subsequent maternal behavior. These changes can also have transgenerational effects [7].

The decision to include the word "nurture" in the title for the intervention in this study was made with careful consideration. Nurture has long been associated in the lay community with a wide and complex range of mother and family environmental influences that are important to infant and child development. Yet, the term nurture remains loosely defined and largely misunderstood in modern society. Perhaps because of this, nurture as the subject for serious study has come to be viewed by a large segment of the scientific community with skepticism or dismissal. Increased demand for evidence-based practice and for simple quantifiable interventions has resulted in a reductionist approach to treatments, and studies testing the effects of interventions have become simpler as data has increased in quantity and has become more complex. As a consequence, few studies have viewed the nurture phenomenon in its breadth and complexity using a multi-disciplinary approach. The purpose of this trial is to address these shortcomings of NICU intervention studies. That is, we are attempting to study the complex multi-variable nurture phenomenon by keeping focused on the biology of development and by approaching nurture through its individual measurable components. In doing so, we hope that this study will lead to a more specific and comprehensive understanding of the word nurture in the public realm and a new appreciation of the concept in the scientific community.

For premature infants in isolettes in the NICU, we are trying to alleviate the multifaceted consequences of nurture deprivation revealed by studies of mother-infant separation in animal models [83-86]. Accordingly, we are enhancing the infant's exposure to the fundamental components of nurture, including maternal odor, touch and voice, and the warmth and tactile experiences of feeding and skin-to-skin contact. Mothers of NICU babies also experience the effects of separation; thus, our intervention is also designed to increase maternal exposure to her infant through the *Calming Cycle *interactions, with the goal of promoting biological and behavioral effects that are contingent upon normal co-regulatory interactions.

Based on the literature and on the extensive clinical experience of the first author, early introduction of repeated mother-infant sensory interactions is expected to alleviate maternal depression, anxiety, and guilt as well as lessen infant aversion to contact that stems from both separation/isolation and the many stressful medical procedures performed as life-saving interventions. The *Calming Cycle *is expected to have global and specific effects on both mother and infant. We hypothesize that repeated engagement of the mother and her infant in the *Calming Cycle *will facilitate the effectiveness of co-regulation (as measured by specific neurobehavioral, physiological and emotional indices) and have immediate and long-term beneficial effects for both. Further, we propose that the *Calming Cycle *provides a basis for helping mothers learn and integrate into their behavioral repertoire a means to initiate interactions with their infants and to respond in ways that maximize states of calm and minimize states of apparent discomfort.

### Potential limitations

There are several limitations to this study. Comparing outcomes in two treatment groups with different patterns of care taking place on the same intensive care unit creates the potential for interactions between participants that can lead to unintended alterations in the treatment actually delivered and in the health of the participants, which, in turn, can affect the outcome measures themselves. For example, whereas the medical and nursing staff is explicitly blind to group assignment, they too may become aware of group status by witnessing NS activities in the FNI group. However, it should be noted that patients in both study groups are intermixed in the intensive care unit among a far greater number of non-study infants. The study NICU census averages 70 infants, with 10 being the maximum number of study infants at any one time, so that the probability of such interactions is low. However, in order to assess the possibility or extent of unintended alterations in treatment, we have included questionnaires for nursing staff and mothers as well as quantitative measures of the specific calming interactions actually taking place between the mothers and infants in both groups.

Another limitation is variation in infant health. Extensive data on infant health is recorded on the unit and differences between groups in rates of infection, medical procedures necessary, and oxygen requirement may influence the infant's availability for intervention or the outcome measures, independent of the intervention. It also should be noted that the mother's availability for spending time in the NICU is limited by other obligations, such as work or other children at home. This factor, however, should not differ significantly between groups. In summary, the NICU is such a busy place that we believe interactions between mothers in the two groups regarding the maternal care differences should be minimal.

To reduce the bias potentially associated with a randomized controlled trial of this size in a modern NICU, the following criteria developed by the Cochrane Collaboration for evaluation of intervention studies [87] will be adopted: (1) the sequence generation of allocating subjects will be random; (2) group designation will be concealed until after consent is obtained and the first set of questionnaires is administered; (3) the blinding of participants, research and clinical staff, and outcome assessments will be achieved to the extent possible; 4) outcome data will be complete; (5) outcome reporting will not be selective.

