**Methods:**

This study is a randomized controlled trial (RCT) with blinded assessment comparing Standard Care (SC) with a novel Family Nurture Intervention (FNI). FNI targets preterm infants born 26-34 weeks postmenstrual age (PMA) and their mothers in the NICU. The intervention incorporates elements of mother-infant interventions with known efficacy and organizes them under a new theoretical context referred to collectively as calming activities. This intervention is facilitated by specially trained Nurture Specialists in three ways: 1) In the isolette through calming interactions between mother and infant via odor exchange, firm sustained touch and vocal soothing, and eye contact; 2) Outside the isolette during holding and feeding via the *Calming Cycle*; and 3) through family sessions designed to engage help and support the mother. In concert with infant neurobehavioral and physiological assessments from birth through 24 months corrected age (CA), maternal assessments are made using standard tools including anxiety, depression, attachment, support systems, temperament as well as physiological stress parameters. Quality of mother-infant interaction is also assessed. Our projected enrolment is 260 families (130 per group).

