Mothers complete initial assessments after consent and families are then assigned to the FNI intervention group or the SC group using a randomized block design. For randomization, six group assignment cards (3 FNI: 3 SC) are placed in envelopes and sealed. The envelopes are shuffled, numbered and placed in a packet prior to use. The RA withdraws an envelope from the packet to determine group assignment. Within 1 to 2 days of consenting, mothers assigned to the FNI group meet with a Nurture Specialist (NS) designated to facilitate the intervention and begin to carry this out, as described in the Intervention Methods section below. Mothers of infants assigned to the SC condition receive NICU standard care as described in the Standard Care section below. Twins are "clustered" for purposes of randomization, with both infants being assigned to the same group along with the mother.

To determine the total sample size necessary to ensure statistical power of not less than 0.8 to detect differences between group means, we considered the detectable difference for each of the primary outcome variables that would be of interest for a successful study result. Our experience and that of others suggested that effect sizes within the 'medium' range would be achievable (i.e., 0.4 to 0.6). Therefore, given the two independent samples created within the RCT design, assuming a significance level of α = .05 for a two-tailed test, we estimate that we will have at least 80% power (1-*β *≥ .80) to detect a difference between groups for effect sizes and total sample sizes as described in Table 1. Experience with the pilot study suggests that we could expect attrition at a rate as high as 40%. To accommodate this, we intend to recruit a total of N = 260 participants from which a final sample size sufficient to detect all differences of interest should be achieved.

**Table 1 T1:** Power analysis

Outcome Measure	PMA	Reference Population *μ *(*σ*)	Detectable Difference |*μ*_FN_-*μ*_SC_|	Effect Size *d*	Total N Required

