### Planned analyses

Descriptive statistics will be derived for all predictor and outcome variables. Family socio-demographic characteristics are not expected to differ by study group, but significance tests will be conducted to confirm the success of the randomization process. Outcomes for the two study groups including infant EEG measures, stress and development, and maternal stress and depression will be compared at each measurement interval (intake, term, 4, 12, 18, and 24 months CA) using independent t-tests for differences between means for continuous data and chi-squared tests for differences between proportions for categorical data. The Bonferroni correction will be applied to account for multiple testing. Longitudinal analyses assessing differences over time will be conducted using repeated measures ANOVA for continuous data and Kruskal-Wallace or Friedman's adaptation of this test for non-parametric data. Generalized linear models will be used to assess the variability in infant development, as measured by Bayley-III Scales at 18 months CA. This variability is explained by repeated maternal and infant psychological and neurological factors after controlling for baseline family socio-demographic characteristics.

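### The bias safeguards promise complete outcome data although the sample size allows for up to 40% attrition, and the named tests would use observed cases only unless the SAP says otherwise

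*Protocol article*

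**What the plan says.** In the protocol article, Potential limitations closes with a list introduced as "the following criteria developed by the Cochrane Collaboration for evaluation of intervention studies", which the trial says it will adopt. The fourth item is "4) outcome data will be complete". It carries no qualifier, whereas the blinding item just before it is limited to what can be achieved.

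The sample size paragraph under Participants draws on the pilot: "we could expect attrition at a rate as high as 40" per cent. It continues: "we intend to recruit a total of N = 260 participants". The abstract gives 130 families per group.

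Physiological Assessments says that the one-hour EEG recording is made only where feasible. EEG at term is one of several primary outcomes listed under Primary and Secondary Outcome Measures. Others include the NNNS and the Bayley-III at 18 months.

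Planned analyses says that outcomes "will be compared at each measurement interval (intake, term, 4, 12, 18, and 24 months CA) using independent t-tests" for continuous data, with a Bonferroni correction. It adds repeated measures ANOVA over time and generalized linear models for the 18-month Bayley-III. It states neither an analysis set nor a rule for missing values.

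**The concern.** A trial that plans for losing up to two families in five cannot also list complete outcome data as a protection against bias. The safeguard describes a property that the design does not expect to have.

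The analysis makes this more than a slip of wording. An independent t-test with nothing added uses the infants who were measured. Classical repeated measures ANOVA goes further and drops anyone with a missed visit. With heavy loss by 18 months, the Bayley-III comparison then rests on the assumption that loss is unrelated to outcome, or distorts both arms by the same amount. The article does not state that assumption, and the safeguard suggests that it is not needed.

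**Working it through.** **Inputs.** Recruitment 260, 130 per group (Participants; abstract). Attrition up to 40% (Participants). Bayley-III at 18 months: SD 14, detectable difference 6.0, total N 174 (Table 1). Two-sided α of .05 and power .80 (Participants).

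**The plan's own figure.** d = 6/14 = 0.4286. A two-sample t-test at two-sided .05 and power .80 needs 174 in total, which agrees with Table 1.

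**What attrition leaves.** 260 × 0.40 = 104 lost and 156 left, or 130 × 0.60 = 78 per arm if loss is equal.

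**Bias of an observed-case comparison.** Let p be the share lost in an arm, and g the mean of the seen infants minus the mean of the lost infants in that arm. The mean over everyone is the seen mean minus p × g, so the seen mean is off by p × g. The bias of the difference, FNI minus SC, is

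bias = p(FNI) × g(FNI) − p(SC) × g(SC).

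It is zero when the two products are equal, for example with equal loss and equal gaps of any size. The article gives no value for p by arm or for g, so every scenario below is an assumption.

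**Equal loss of 40%, gaps differing between arms.** SE = 14 × √(2/78) = 2.24. With no true effect, the rejection rate is P(Z > 1.96 − bias/SE) + P(Z < −1.96 − bias/SE).

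| Between-arm difference in g (assumed) | Bias | Share of 6 points | Rejection rate at nominal 5% |
|---|---|---|---|
| 0 | 0.4 × 0 = 0 | 0% | 5% |
| 5 points | 0.4 × 5 = 2.0 | 33% | 14.5% |
| 7 points | 0.4 × 7 = 2.8 | 47% | 23.9% |

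Five points is 5/14 = 0.36 SD, a sizeable selection difference beside a target of 0.43 SD.

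**Unequal loss, equal gaps.** With 20% lost in FNI, 40% in SC and a gap of 10 points in both, bias = 0.2 × 10 − 0.4 × 10 = −2.0. The size is again a third of the target, but the sign now works against FNI.

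**With a Bonferroni step.** The article does not fix the number of tests. Assuming the seven primary measures it lists (EEG, NNNS, language scale, ASQ, Bayley-III, HRV, cortisol), α = .05/7 = .0071 and the critical value is 2.69. The rejection rate then rises from 0.7% to about 3.6% at a bias of 2.0 and 7.5% at 2.8. It is still several times nominal, but well below the uncorrected figures.

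The SE treats the 78 per arm as independent and ignores twin clustering.

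**The case against.** The fourth item can be read as shorthand for a bias-tool domain, placed among the limitations in an article that openly discloses the 40%. A reader is therefore not misled about expected loss. That softens the matter but does not remove it: the list is worded as commitments, and the adjacent item shows that the authors qualified when they meant to.

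Three stronger readings are tempting, and the documents do not support them.

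- A reader might infer that the plan restricts its tests to families who attend. It does not say so. Observed-case analysis is what the named methods do by default, and the SAP or full protocol may provide otherwise. Silence on missing data in a condensed article is not itself a fault.
- A reader might infer that attrition will shift the primary result by a third of the target difference. No figure in the article yields that. It is one assumed scenario in a range that starts at zero, there are several primary outcomes, and the 40% is tied to no particular visit. The 104 missing Bayley-III scores are a ceiling.
- A reader might infer that contact with the Nurture Specialist keeps FNI families in the trial and so favours FNI. Both arms have the same assessments, and the 18-month visit was timed to the age at which local neonatologists perform the Bayley-III. FNI mothers also commit to at least four one-hour sessions a week, a burden that could raise their loss. The direction is unknown.

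The generalized linear models for the Bayley-III adjust for socio-demographic characteristics. This helps only so far as loss depends on those covariates, and by default these models too use complete cases.

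**Conclusion.** The contradiction stands on the article's own words, and no SAP could make both statements true. The analysis point is conditional: unless the SAP adds something, the t-tests and repeated measures ANOVA use observed or complete cases. They are then unbiased only if loss is unrelated to outcome or acts equally in both arms.

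The size is not known. At 40% loss per arm, and an assumed 0 to 7 points between arms in the seen-minus-lost gap, the bias in the 18-month Bayley-III difference runs from 0 to 2.8 points, or 0 to 47% of the 6-point target. The nominal 5% test then runs from 5% to at most about 24% before any Bonferroni correction. This deserves correction, but it does not show that the result will be biased.

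A separate matter of power should not be confused with this one. The 156 left at 40% attrition fall short of the 174 that Table 1 requires for the Bayley-III, although the article expects "a final sample size sufficient to detect all differences of interest should be achieved".

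**What to change.** Replace the fourth item with a statement that attrition of up to 40% is anticipated and will be reported by arm with reasons. Make it consistent with the sample size paragraph and with the EEG being recorded only where feasible.

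Unless the SAP already specifies an equivalent, analyse the 18-month Bayley-III and the other follow-up outcomes with all randomised families under missing at random. Use a mixed model, or multiple imputation from measures already collected: gestational age, birth weight, socio-demographic characteristics, the CES-D and STAI taken before assignment, and EEG and NNNS at term. Add a delta-adjusted sensitivity analysis that varies the assumed shift in lost infants by arm and reports where the conclusion changes, since missing at random cannot be verified from the observed data.

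The cost is a change of wording, a modest amount of extra analysis and a less favourable stated assurance. No new data collection is needed.

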## Conclusions

This FNI study will provide neurodevelopmental evidence about the importance of early and extensive mother-infant interactions, within the constraints of the NICU. This study will also test the practicability of the Family Nurture Intervention as a means to improve outcomes in prematurely born infants and their families. We are hopeful that the evidence-based methodologies employed in this study will also lead to an improved level of personalized care in the NICU, enhanced family involvement, and a more constructive relationship between the hospital and the community.

## List of abbreviations

AAI: Adult Attachment Interview; ATQ: Adult Temperament Questionnaire; BIS-BAS: Behavioral Inhibition System-Behavioral Approach System; CA: Corrected Age; CES-D: Center for Epidemiological Studies Depression Scale; COPE: Creating Opportunities for Parent Empowerment; FCC: Family Centered Care; FNI: Family Nurture Intervention; KC: Kangaroo Care; MSES: Maternal Self-Efficacy Scale; NICU: Neonatal Intensive Care Unit; NIDCAP: Newborn Individualized Developmental Care Assessment of Preterm infants; NS: Nurture Specialist; NSSQ: Norbeck Social Support Questionnaire; PMA: Postmenstrual Age; PSI: Parental Stress Index; RA: Research Assistant; SC¸ Standard Care.
